### Eligibility criteria

Adult patients scheduled to undergo a major liver resection by either laparotomy or laparoscopy for any indication will be eligible. Major liver resection is defined liberally based on the PRICE-1 pilot RCT [40] as resection or partial resection of at least 3 liver segments, right posterior sectionectomy (segments 6 and 7), central resection of segments 4b/5, or a resection of a full single segment in a patient known to have liver cirrhosis.

Exclusion criteria were adopted and modified from Jarnagin et al. [49]. Individuals who meet one or more of the following criteria will be excluded from the study: (1) age <18 years; (2) preoperative hemoglobin <100 g/L; (3) glomerular filtration rate (GFR) <60 mL/min; (4) platelets count <100 × 10^9^/L; 5) active cardiac conditions (defined as unstable coronary syndromes, severe valvular disease, myocardial infarction within the past 6 months, or hypertrophic cardiomyopathy); (6) history of significant cerebrovascular disease (clinically-significant cerebrovascular accident within the past 6 months or severe carotid stenosis >70%); (7) history of significant peripheral vascular disease (non-revascularized with regular/ongoing claudication); (8) pregnancy; (9) refusal of blood product transfusions; (10) presence of active infection; (11) preoperative autologous blood donation; (12) planned intraoperative use of cell salvage; (13) inability to comply with the trial follow-up at 30 and 90 days; and (14) previous participation in the trial in the case of redo liver resections.

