#### Secondary outcomes

Secondary outcomes (Table 1) will also be considered up to 30 days and include:Proportion of patients receiving other allogeneic blood products (FFP, cryoprecipitate, platelets, and albumin) and the number of units of transfused allogeneic blood products.Blood loss, measured in the operating room using the methodology employed in the feasibility trial [40]. All suctioned fluids will be recorded. All unused irrigation fluids will be similarly measured and subtracted from the total irrigation fluid provided for the case. All surgical sponges will be weighed using a dedicated zeroed scale and converted to milliliters from grams using the specific gravity of blood. Total blood loss will thus be measured as: suctioned fluids + sponge volume − irrigation fluids. Blood loss will also be estimated using the preoperative and day 2 hemoglobin values (accounting for any transfused allogeneic blood) using the Flordal equation [56, 59].All intraoperative and postoperative adverse events, graded according to the Clavien-Dindo Classification of Surgical Complications [57] and the Comprehensive Complication Index [58]. In addition, end-organ ischemic complications (renal [60], cardiac, cerebral, hepatic, mesenteric) will be specifically monitored, graded, and reported.Intraoperative physiologic parameters (CVP, pulse pressure variation [PPV], cardiac index, total peripheral vascular resistance index, mean arterial pressure [MAP], urine output). All parameters will be measured at the onset of surgery after induction of anesthesia, and at different time points during the intraoperative period.Mortality at 30 and 90 days.Oncologic outcomes will be examined retrospectively approximately 3 years following completion of the study. A separate study protocol will be devised to examine these outcomes.

**Table 1 Tab1:** Outcome measures and their evaluation timepoints

Outcome measures	Timepoints of evaluation

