**Blood loss**: Three methods will be used independently. In the operating room, all blood and fluid aspirated from the abdomen will be measured accurately using graduated suction containers. The amount of irrigation fluid will be carefully monitored and recorded. The weight of all surgical sponges will be measured. This information will be used by (1) the surgeon and (2) anesthesiologist to independently visually estimate blood loss, as is commonly done in clinical practice. In parallel, intraoperative blood loss will also be (3) calculated based on the Flordal equation [56], using preoperative and day 2 hemoglobin levels.	Day 0 Day 2
Packed RBC transfusion	Day 7 Day 30
Other blood product transfusion rate (FFP, cryoprecipitate, albumin, others)	Day 7 Day 30
Overall morbidity rate, major morbidity rate (Clavien-Dindo grade 3a or greater [57]), Comprehensive Complication Index [58] and any perioperative adverse events.	Day 7 Day 30
Mortality	Day 30
Surgeon perception scale (Additional file 3)	Day 0
Intraoperative physiologic parameters (CVP, PPV, total peripheral vascular resistance index, MAP, urine output)	Measured at the onset of surgery (after induction of anesthesia) at various time points

*CVP* Central venous pressure, *FFP* Fresh frozen plasma, *MAP* Mean arterial pressure, *PPV* Pulse pressure variation, *RBC* Red blood cell

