### Statistical analysis

Our analyses will estimate a modified intention-to-treat effect, such that patients who were randomized in the operating room but did not undergo liver resection due to unresectability will not be included in the analyses. A blinded committee of liver surgeons will adjudicate each post-randomization exclusion. This will ensure that only cases of liver resection abandoned due to unresectability will be excluded from analysis. All other patients who have had protocol deviations (e.g., having an unplanned minor rather than major resection) or crossover (e.g., inability to achieve a full 7–10 mL/kg phlebotomy) will be analyzed within their allocated arm based on an intention-to-treat principle.

Continuous variables will be reported using means and standard deviations, or medians and interquartile ranges, as appropriate. Categorical variables will be reported as frequencies and percentages.

For the primary outcome of 30-day cumulative incidence of any perioperative RBC transfusion, the risk ratio and risk difference will be presented with their respective 95% confidence intervals. Both unadjusted and adjusted effect estimates will be presented. We will fit multivariable generalized linear models using generalized estimating equations (GEE) with an exchangeable correlation matrix with model-based (non-robust) standard errors to estimate an adjusted risk ratio and relative risk, accounting for center effect (clusters). We will incorporate important prognostic covariates (age, sex, preoperative anemia, indication for surgery, magnitude of liver resection, extra-hepatic procedures). Although safeguards are in place to ensure complete data acquisition throughout the trial, missing data for covariates will be handled using multiple imputations by chained equations, where multiple imputed datasets will be pooled to generate final estimates using Rubin’s rules. We will also conduct a complete case analysis to evaluate the potential effect of the missing at random assumptions underlying missing data. Hypothesis testing for the primary endpoint will be carried out at a two-tailed alpha level of 0.05.

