For secondary outcomes, both unadjusted and adjusted measures of effect will be presented. Risk ratios and mean differences with 95% confidence intervals will be presented for dichotomous and continuous data, respectively. We will use similar models with GEEs and model-based (non-robust) standard errors to generate adjusted effect estimates, incorporating the same set of covariates as for the primary outcome. For secondary outcomes and analyses, no adjustment will be made for multiplicity.

Subgroup analyses will be conducted based on known risk factors for transfusion in liver surgery: preoperative anemia (larger treatment effect expected with anemia), indication for surgery (larger treatment effect expected with primary liver cancers), and magnitude of liver resection (larger treatment effect expected for extended resections) [61]. An interaction test will be used between each subgroup variable and the treatment group within GEEs estimating risk differences. Published criteria will be used to evaluate the plausibility of the subgroup effects [65].

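### The adjusted models for intraoperative physiology omit the parameter's own post-induction value, which gives up precision on the mechanistic outcomes but causes no bias

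*Protocol article*

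**What the plan says.** The Statistical analysis section of the protocol article lists the adjustment variables for the primary outcome as "important prognostic covariates (age, sex, preoperative anemia, indication for surgery, magnitude of liver resection, extra-hepatic procedures". For secondary outcomes it prescribes similar GEE models, "incorporating the same set of covariates as for the primary outcome". No outcome-specific baseline is named.

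The secondary outcomes include "Intraoperative physiologic parameters (CVP, pulse pressure variation [PPV], cardiac index, total peripheral vascular resistance index, mean arterial pressure [MAP], urine output", and the article says of them: "All parameters will be measured at the onset of surgery after induction of anesthesia, and at different time points during the intraoperative period". A first value of each parameter is therefore part of the planned data.

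On haemoglobin, the list names anaemia. The same section uses the term as a subgroup factor: "preoperative anemia (larger treatment effect expected with anemia". The measured concentration is also needed. The Eligibility criteria exclude "preoperative hemoglobin <100 g/L", and under Secondary outcomes "Blood loss will also be estimated using the preoperative and day 2 hemoglobin values".

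**The concern.** When a continuous outcome is measured before and after an intervention, its own earlier value is usually among the strongest predictors of the later one. A covariate rule that carries over the primary-outcome set leaves that predictor out of every physiologic model.

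These outcomes matter because they bear on mechanism. The Background proposes that phlebotomy works through a mild-to-moderate fall in CVP, and both arms aim for the same CVP ceiling (Experimental intervention; Control intervention). The contrast between arms may therefore be modest, and a wider interval than necessary could leave the mechanistic question open. Adjustment would also absorb chance imbalance in the starting values.

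The haemoglobin question is of the same kind but smaller: a category carries less information than the concentration behind it.

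**Working it through.** **The plan's own figure.** For 20% versus 10%, two-sided 5% alpha and 80% power, with pooled variance under the null:

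n = [1.960·√(2·0.15·0.85) + 0.842·√(0.20·0.80 + 0.10·0.90)]² / 0.10² = [0.990 + 0.421]² / 0.01 ≈ 199 per arm.

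The allowance for 5% non-compliance is 1/(1 − 0.05)² = 1.108, and 398 × 1.108 ≈ 441 against 440 stated. The sample size reproduces. It assumes no gain from covariates.

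**Is the post-induction value pre-intervention?**
- Secondary outcomes: the first measurement follows induction.
- Allocation concealment: allocation is revealed once anaesthesia has been given and all lines are in.
- Experimental intervention: phlebotomy follows allocation and is completed before transection.

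The sequence points to a measurement before phlebotomy, but no sentence says so. This needs confirming, because adjusting for a value taken after blood withdrawal has begun would remove part of the effect being estimated.

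**Precision forgone, physiology.** Adding a baseline with within-arm correlation ρ to the later value (given the covariates already in the model) multiplies the residual variance by 1 − ρ² and the standard error by √(1 − ρ²). The article gives no ρ, so a range is assumed:

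| ρ (assumed) | Variance left | Variance saved | SE factor | 440 patients act as |
|---|---|---|---|---|
| 0.3 | 0.91 | 9% | 0.95 | 440/0.91 ≈ 484 |
| 0.5 | 0.75 | 25% | 0.87 | 440/0.75 ≈ 587 |
| 0.7 | 0.51 | 51% | 0.71 | 440/0.51 ≈ 863 |

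The last column applies only to a parameter with a baseline in all 440 patients.

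**Haemoglobin, primary outcome.** If a normally distributed covariate is split so that a fraction q is anaemic, the share of its linear information kept is φ(c)²/[q(1 − q)], where c is the cut-point on the standard normal scale. This is 49%, 58%, 62% and 64% for q = 20%, 30%, 40% and 50% (assumed).

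The effect on the treatment estimate was simulated: 440 patients, 20% versus 10%, 4,000 runs, 40% anaemic, with haemoglobin as the only covariate. The model was logistic, standardised to a risk difference. Power is for the treatment coefficient in that model.

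| Odds ratio per SD lower haemoglobin (assumed) | Variance, continuous ÷ category | Power, category | Power, continuous |
|---|---|---|---|
| 1.5 | 0.996 | 85.5% | 85.9% |
| 2.0 | 0.973 | 85.4% | 86.2% |
| 2.5 | 0.966 | 86.6% | 87.7% |

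The gain is about 0.4 to 3.5% of variance and roughly 0.4 to 1.1 points of power. The other planned covariates were not simulated; they may already explain part of what haemoglobin explains.

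**The case against.** Several objections carry weight.

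**Coverage.** The section on common anaesthetic management requires a central venous catheter in all patients, but leaves the arterial catheter and cardiac-output monitoring to the anaesthesiologist. Baselines for PPV, cardiac index and vascular resistance may be missing in many patients. Urine output is cumulative, so an early value may say little. The case is secure mainly for CVP and MAP. This stands and limits the fix.

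**Correlation.** Both arms target a low CVP, and in the phlebotomy arm haemodynamic disturbance is managed with vasopressors. Active titration can weaken the link between first and later values, which is why 0.3 belongs in the range.

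**Left to the analysis plan.** The article says the models are similar, not identical, and an analysis plan could set out how repeated measurements are handled. That is fair for the modelling of time points. It does not dispose of the point, because the article states a covariate rule for the secondary outcomes and that rule leaves the baseline out.

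**Haemoglobin.** A reader might infer that the protocol dichotomises haemoglobin in the primary model. It does not say that: no coding or cut-off is given for any covariate, and the subgroup wording does not fix the form used for adjustment. Nor is continuous haemoglobin free of cost. About 0.15 × 440 = 66 events are expected, and a linear term on the risk-difference scale can give fitted risks below zero. For example, assume a mean of 132 g/L, an SD of 14 and a logit slope of 0.4 per 10 g/L. The risk then falls by about 0.4 × 0.15 × 0.85 ≈ 5 points per 10 g/L, so a 10% risk at the mean reaches zero near 152 g/L, with roughly 8% of patients above that.

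**Conclusion.** The point holds for the physiologic outcomes and is one of efficiency. The stated covariate rule omits a predictor that the trial plans to record, at a cost of 9% to 51% of residual variance for assumed correlations of 0.3 to 0.7. The size rests entirely on that assumption and on the first measurement preceding phlebotomy.

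Two stronger readings are not supported. A reader might infer bias from uncorrected baseline imbalance; randomisation keeps the estimates valid, and the confidence intervals already allow for chance imbalance. A reader might also infer that planned power for the primary outcome is lost; the 199 per arm was calculated without any covariate gain.

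The haemoglobin point is conditional and minor. It applies only if anaemia enters the adjusted models as a category, and its effect on the primary result is small.

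**What to change.** In the secondary-outcome paragraph of the Statistical analysis section:

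1. Add the parameter's own onset-of-surgery value as a covariate in the models for CVP and MAP, and in those for PPV, cardiac index and vascular resistance where that value was measured. Exempt urine output.
2. State that this value is taken before phlebotomy starts, after checking that it is.
3. Optional: state how preoperative anaemia enters the adjusted models. If as a category, use measured haemoglobin as a continuous term instead and keep the category for the subgroup analysis. Specify the functional form, with few parameters given about 66 events, and how fitted risks outside 0 to 1 in the risk-difference model will be handled.

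Items 1 and 2 take a sentence or two and need no measurement beyond those planned. Item 3 needs a little more modelling detail. Recruitment was still open when the article appeared, so these changes could be fixed before the final comparison by arm.

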### Data monitoring

The PRICE-2 Steering Committee will be comprised of the principal investigator (PI), all co-investigators (Co-I), and the trial coordinator. The Steering Committee will communicate regularly and will meet as needed. The Committee will implement the trial, review recruitment milestones, and manage any evolving concerns related to trial procedures. An independent DSMB will be appointed and will have expertise in surgery, anesthesiology, biostatistics, and clinical trials. The roles, responsibilities, and reporting of the DSMB, including the interpretation of the interim analysis and adverse events, will be adapted from the DAMOCLES Charter [66].

Three interim analyses will be completed and reported to the Data Safety Monitoring Board (DSMB). The first interim analysis will take place after 100 patients and will examine accrual and adverse events data. The second interim analysis will be conducted after 200 patients and will examine accrual, adverse events, and the primary efficacy outcome. A conservative Haybittle-Peto boundary (*p*<0.001) [67] will be utilized. The third interim analysis will be conducted after 300 patients and will examine accrual and adverse events. The final analysis will be conducted once all 440 patients have been randomized, have had a liver resection, and have been followed to 30 days following surgery, based on the modified intention-to-treat principle.

Study site monitoring will take place remotely at the start of recruitment for each site, as well as upon completion of accrual. Ongoing data monitoring will be conducted and data queries that arise, as well as any issues related to incomplete data, will be addressed on an ongoing basis with study sites. Finally, a formal trial audit plan has been created. A formal audit of the trial will be conducted by the study sponsor and will include complete review of the coordinating center study file, review of a small proportion of participant records, and review of the study files of participating sites.

### Adverse events

Published data from our group and others have not documented any significant differences in overall postoperative complications, end-organ ischemic complications (renal, cardiac, cerebral, hepatic, and mesenteric), or perioperative mortality between HP and usual care [34, 39, 41–45, 48]. Similarly, PRICE-1 [40] and two other small trials [46, 47] noted no significant differences in any adverse event metric. Nevertheless, low-volume phlebotomy could potentially lead to any physiologic effect associated with blood loss. These effects could have implications for any major organ system due to decreased perfusion (e.g., myocardial ischemia, cerebrovascular accident, acute renal failure, hepatic insufficiency). These risks exist with liver surgery, whether HP is performed or not, due to potential significant blood loss. To be considered fit for liver surgery, patients cannot have excessive comorbid illnesses that could be grossly exacerbated by the operation. The patient population that is thus considered for surgery is a relatively fit one that can tolerate HP. Furthermore, the inclusion and exclusion criteria that have been built in this protocol exclude those at a greater risk of adverse event associated with decreased organ perfusion. Other potential risks associated with HP pertain to the collection of whole blood and its auto-transfusion at the end of surgery. There is a potential risk for clerical error with the blood. Similarly, there is a theoretical risk of bacterial contamination of the collection bag, tubing, and, whole blood. To minimize these risks, all study procedures have been developed conjointly between surgery, anesthesiology, and the Transfusion Medicine (TM) department at our center and have been agreed upon by participating centers. The collection bags will be provided by TM, labelled with the patient identifier, and handled and processed in the same manner as any other blood product in the operating room. This procedure will allow for the safe handling of all blood specimens, in accordance with all protocols already in place at each study center

The PI or co-investigators will determine if any serious and unexpected adverse events occur from randomization to postoperative day 30. The SC, PI, or co-investigators will examine changes in laboratory values, vital signs, and clinical data, and will determine if the changes are clinically important and different from what is expected during treatment of participants having undergone hepatic surgery and general anesthesia. As perioperative complications represent an important secondary outcome in this trial, adverse events (AEs) will be carefully monitored and recorded. AEs can generally be described as any unfavorable and unintended sign, symptom, or disease temporarily associated with the treatment, whether or not related to the study treatment.

For this trial, any surgical, medical, or anesthesia-related AE that deviates from the usual postoperative course of patients undergoing major liver resection will be collected and recorded in the study AE Source Form by the PI, Co-I, or SC. The PI or Co-I will then assign a grading to this AE based on the Clavien-Dindo classification of perioperative complications [57]. The following will not be considered AEs:*Intraoperative*: bleeding (unless deemed unusually severe by the surgeon), hypotension (unless deemed unresponsive to usual mitigation strategies), oliguria*Postoperative*: pain, hypotension (unless deemed unresponsive to usual mitigation strategies), oliguria (unless associated with acute kidney injury), nausea or vomiting (unless related to ileus or obstruction, or if refractory), sore throat, muscle aches, pruritus, chills, chest pain (unless deemed to be related to a defined AE such as acute coronary syndrome), anemia not requiring transfusion, electrolyte disturbances (unless refractory to usual replacement therapy)

Any AE that is graded as Clavien-Dindo grade 3a or greater will be considered a severe adverse event (SAE). SAEs will be recorded on the study SAE Case Report Form. All SAEs will be further assessed by the PI or Co-Is for expectedness and relatedness to the study procedures. On that basis, unexpected SAEs will be reported to the REB.

### Dissemination and protocol amendments

Any protocol amendment will be submitted to the relevant REBs for approval before implementation and registered at ClinicalTrials.gov. Once REB approval is obtained at the coordinating center, the PI will brief all relevant parties’ site investigators and coordinators on the amendments, and a copy of the amended protocol will be provided. Participating sites will then seek approval of the amendment from their respective hospital’s REB before implementing the updated protocol. Study results will be disseminated using peer-reviewed publications.

## Discussion

### Perspectives of the study

PRICE-2 is a complex interventional trial conducted in the operative environment. There are several practical challenges associated with carrying out trials of this nature, such as “defining, developing, documenting, and reproducing complex interventions” [68]. Each challenge has been carefully thought out and addressed in the study protocol. First, this study requires a significant degree of cooperation among team members (surgeons, anesthesiologists, nurses, blood bankers, clinicians in charge of PBM programs). Second, components of the intervention have to be sufficiently defined to allow reproducibility but must remain pragmatic enough to allow for patient management in real time in the operating room. Third, numerous co-interventions can influence the primary outcome of RBC transfusion, as well as the associated secondary outcome of blood loss. In the interest of striking a judicious balance, the investigators have chosen to focus on the most important co-interventions, namely administering tranexamic acid to all patients, disallowing other CVP-lowering techniques (e.g., diuretics, vasodilators, local anesthetic within epidurals), and disallowing cell salvage use. Fourth, the investigators seek to include all patients at high risk of bleeding by introducing a liberal definition of major hepatic resection. Finally, learning curve considerations have led the investigators to limit opening this trial within centers with previous HP experience.

The results of this randomized control trial will provide high-quality evidence regarding the use of hypovolemic phlebotomy in major liver resection and its effects on RBC transfusion. If proven to be effective, this intervention could become standard of care in liver operations internationally and become incorporated within perioperative patient blood management programs.

